Assess the effectiveness of presumptive anti-relapse and transmission-blocking therapy with weekly low-dose primaquine (22.5 mg)^a^	Incidence of *P. vivax* recurrent infection and PCR-corrected *P. falciparum* recrudescence^a^ PCR-corrected absence of gametocytemia^a^
Evaluate the safety and tolerability of blood-stage antimalarials and weekly low-dose primaquine at 12 weeks versus 8 weeks in treated MMP and FSAT volunteers, respectively	Number of hemolytic events or other serious adverse events in participants over 13 years of age receiving primaquine
Assess level of antimalarial drug resistance at the selected study sites	Number of all-species malaria recurrence, established molecular markers of drug resistance, and clinical failure rates based on WHO criteria
Define the proportion of asymptomatic carriers of malaria in the study population	Cumulative incidence and incidence density of PCR-corrected parasitemia and submicroscopic parasitemia in each arm
Define the epidemiology of malaria infection in volunteers developing malaria	Cumulative incidence and incidence density of parasitemia
Compare the sensitivity and specificity of the currently recommended malaria rapid diagnostic test of choice in Cambodia with RT-PCR	Retrospective assessment of the proportion of asymptomatic carriers that would have been missed by each test and an estimate of the incremental cost-effectiveness of each test
Compare sensitivity and specificity of two currently available rapid diagnostic tests to detect moderate to severe G6PD deficiency using quantitative G6PD testing as the reference standard	Retrospective assessment of the proportion of persons with moderate to severe deficiency who would have been missed with each screening modality, and an estimate of the cost-effectiveness of each test
Describe population demographics to include the acceptability of FSAT, malaria prophylaxis, and use of vector control measures among participants, including willingness to participate in future malaria elimination campaigns	Descriptive analysis of participants’ responses to survey questions pre and post study regarding FSAT, malaria prophylaxis, and use of vector control measures

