## Methods/design

### Study design

We are conducting a two-arm, cluster-randomized, open-label controlled trial of MMP with t3-day DHA-PIP and weekly PQ compared to focused screening and treating (FSAT) following current national treatment guidelines. Participants in the MMP arm receive a monthly 3-day course of fixed-combination tablet containing 40 mg of dihydroartemisinin and 320 mg of piperaquine phosphate for three consecutive months. Those aged 13 years and older receive low-dose weekly PQ (22.5 mg) therapy to prevent malaria transmission for 12 weeks. Participants in the FSAT arm are screened with highly sensitive polymerase chain reaction (PCR) methods, and all those testing positive for malaria receive therapy with first-line antimalarials following current national treatment guidelines. At the time of protocol development, artesunate-mefloquine combination therapy is the first-line treatment for *P. falciparum* in provinces with known antimalarial resistance, with a single, low dose of PQ (15 mg) to prevent malaria transmission. For participants in the FSAT arm with *Plasmodium vivax* malaria, the recommended treatment for asexual parasitemia is DHA-PIP. All patients with *P. vivax* in the FSAT arm receive treatment with 15 mg of PQ daily for 14 days if G6PD normal, or 45 mg weekly if G6PD deficient.

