### Treatment intervention

Volunteers randomized to MMP arm aged 13 years and older receive a monthly 3-day treatment course of (DHA-PIP; 360/2880 mg) for 3 months. They will also receive a weekly dose of 22.5 mg of PQ for 12 weeks. Children of 12 years of age or less will receive only a monthly 3-day weight-based treatment dose of DP for 3 months without PQ treatment. In the MMP arm, symptomatic patients or microscopy-confirmed parasitemia in the first 3 months are considered a failure of prophylaxis and treatment is given according to the national treatment guidelines. If the volunteer has parasitemia detectable by PCR only and is symptom free at monthly follow-up, the study treatment with monthly DHA-PIP is continued for 3 months as outlined for the MMP arm. To reduce phlebotomy requirements for G6PD testing and potential hemolytic risk in children, PQ is not be administered to those less than 13 years old.

Volunteers randomized to the focused screening and treatment (FSAT) arm are treated according to current national malaria treatment guidelines if they test positive for malaria based on blood smear and/or real-time PCR results during monthly follow-up. In the FSAT arm, all volunteers with parasitemia detectable with PCR receive antimalarial treatment, even if they are symptom- free.

At the time of protocol development, national treatment guidelines for areas of known piperaquine resistance, to include the designated study regions, recommended a 3-day course of artesunate and mefloquine (A + M) and a single 15-mg dose of PQ for acute *P. falciparum*, or DP for blood-stage *P. vivax* infection. Elimination interventions are carried out monthly during the first 3 months after enrollment, and then followed by 3 months of additional malaria assessment by smear and PCR diagnosis with malaria treatment as necessary following current national treatment guidelines (Fig. 1, Table 2, Fig. 2). Those febrile but negative for malaria are referred for evaluation and treatment of alternative diagnoses.

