**Fig. 1 Fig1:**
[figure not shown]
Study flow diagram

**Table 2 Tab2:** Table of times and events for adults and children over 12 years of age

Event	Screen/enroll day 1	Day 3^3^	Day 30^7^	Day 60^7^	Day 90^7^	Day 120^7^	Day 150^7^	Day 180^7^	Malaria diagnosis/ recurrence^2^
a. Informed consent	X								
b. Medical history	X								
c. Physical exam	X								X
d. Brief clinical evaluation and vital signs^1^			X	X	X	X	X	X	X
e. Malaria RDT, DBS, smear and PCR genotyping^6^	2 mL		1.5	1.5	1.5	1.5	1.5	1.5	1.5 mL
i. CBC	1 mL	1 mL^3^							
k. Molecular resistance markers^2^									6 mL
l. G6PD RDT, fluorescent spot, quantitative testing	1.5 mL								
m. Gametocyte PCR	2.5 mL		2.5	2.5	2.5	2.5	2.5	2.5	2.5 mL
n. Urine pregnancy test (women of child-bearing age)	X		X	X					X
o. Malaria treatment^4,5^	X		X	X					X
Daily phlebotomy (mL)	7	1^3^	4	4	4	4	4	4	10
Cumulative phlebotomy (approximately mL)	7		11	15	19	23	27	31	41

^1^Brief clinical evaluation includes an interval medical history, vital signs and a directed physical exam as indicated

^2^Performed only for volunteers with smear-positive malaria. Those with PCR-positive malaria will be treated following national guidelines but will not have blood drawn for molecular markers of resistance

^3^To be drawn for G6PD-deficient volunteers only. All G6PD-deficient volunteers with > 10% of Hgb or HTC drop on D3 will have CBC on day 7

^4^Patients screening positive on microscopy and/or PCR for *P. falciparum* malaria in the FSAT arm will receive currently recommended blood-stage antimalarials under published national treatment guidelines as well as single, low-dose primaquine (15 mg). Volunteers with *P. vivax* will be treated with the currently recommended blood-stage agent (DHA-PIP), as well as primaquine – G6PD-normal volunteers will receive 15 mg daily for 14 days, while G6PD-deficient volunteer will receive 45 mg × 8 weeks. All volunteers in the MMP arm will receive a fixed-dose 3-day course of DHA-piperaquine at 0, 24 and 48 h starting on days 1, 30, and 60, and a weekly 22.5-mg dose of primaquine for 12 weeks. All therapy will be directly observed

^5^For all volunteers with recurrent malaria, rescue therapy will be with the recommended agent(s) per national guidelines

^6^May be repeated as medically indicated (e.g., if patient is malaria-positive or otherwise ill on enrollment). An additional 0.5 mL will be collected on the day of enrollment for baseline G6PD genotyping

^7^Time window of ± 7 days

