### Clinical procedures

Following documentation of informed consent/assent and determination of eligibility, a study physician completes an initial medical history and physical examination (Table 2). Volunteers aged 13 years and older have a rapid diagnostic test (RDT) for malaria, thick and thin blood films to estimate both sexual and asexual parasite densities, and malaria PCR diagnosis. Additional laboratory testing includes a complete blood count (CBC); an estimate of G6PD activity using quantitative testing to be compared with fluorescence and commercially available point-of-care testing; G6PD genotyping; real-time PCR to detect gametocytes; and analysis of molecular markers of resistance for those malaria positive at intake. Children aged 12 years and under have only rapid malaria diagnostic testing, malaria smears and PCR to detect submicroscopic parasitemia, with other testing deferred in children to reduce phlebotomy burden. Children less than 13 years of age are not tested for G6PD deficiency as they are not treated with PQ under this protocol. G6PD-deficient volunteers 13 years and older are counseled regarding the diagnosis, and have a repeat CBC on day 3 (± 1 day) following PQ treatment with repeat testing on day 7, if they have a greater than 10% drop in their hemoglobin or hematocrit, or at any time there are clinical signs of hemolysis.

All volunteers are followed monthly thereafter or at any time that they present with symptoms of suspected malaria, with a brief clinical evaluation and malaria diagnostics to include PCR assays for asexual and sexual parasites. Malaria-positive volunteers aged 13 years and older have additional tests for molecular markers of resistance. At these times, a swatch is taken from the volunteer’s uniform or clothing for repellency monitoring.

At the conclusion of the 180-day (− 2 to + 3 days) follow-up period, volunteers have blood drawn for malaria smears, RDTs, asexual blood-stage and gametocyte PCR diagnosis. If infection is noted at discharge, volunteers will continue to be followed until resolution of infection.

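### Table 1's 12- versus 8-week primaquine safety contrast matches no pair of regimens in the trial: the only 8-week course is twice the weekly dose and goes only to G6PD-deficient P. vivax cases

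*Protocol article*

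**What the plan says.** Table 1 (Aim and objectives) has a secondary objective on the safety and tolerability of blood-stage antimalarials and "weekly low-dose primaquine at 12 weeks versus 8 weeks in treated MMP and FSAT volunteers, respectively". The matching endpoint is "Number of hemolytic events or other serious adverse events in participants over 13 years of age receiving primaquine". The row directly above it in Table 1 attaches a dose to the same phrase: "presumptive anti-relapse and transmission-blocking therapy with weekly low-dose primaquine (22.5 mg").

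The regimens are set out elsewhere in the article:

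- **MMP, aged 13 or older** (Treatment intervention): "They will also receive a weekly dose of 22.5 mg of PQ for 12 weeks". G6PD testing states that deficiency, including severe deficiency, does not bar enrollment.
- **FSAT, P. vivax** (Study design): these patients "receive treatment with 15 mg of PQ daily for 14 days if G6PD normal, or 45 mg weekly if G6PD deficient". Table 2, footnote 4 adds the duration of the weekly course: "G6PD-deficient volunteer will receive 45 mg × 8 weeks".
- **FSAT, P. falciparum** (Study design; Table 2, footnote 4): one 15 mg dose.

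On blood counts after dosing, Table 2, footnote 3 says of the day-3 CBC: "To be drawn for G6PD-deficient volunteers only". Clinical procedures likewise gives deficient volunteers aged 13 or older a day-3 CBC "following PQ treatment with repeat testing on day 7, if they have a greater than 10% drop" in hemoglobin or hematocrit, and also allows testing whenever hemolysis is clinically evident. Table 2 lists no later CBC.

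**The concern.** The objective reads as a comparison of two durations of one regimen. If the regimens differ in more than duration, a difference in event counts, or the lack of one, says nothing specific about whether 12 weeks is as safe as 8.

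The article means to use these data. The Discussion section on primaquine expects them to help define minimum G6PD screening requirements. Limitations says adverse event data will be used to judge whether the approach is feasible. Both uses need events separated by G6PD status and by what was given. The Discussion also cites an 8-week precedent for 22.5 mg weekly, so weeks 9-12 of the MMP course go beyond the cited experience. Those are the weeks on which a 12- versus 8-week statement would be most wanted.

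**Working it through.** The article gives no event rate, sample size or power for this endpoint, so there is no figure to reproduce. The check sets the regimens side by side.

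| Group | Regimen | Total primaquine | Recipients |
|---|---|---|---|
| MMP | 22.5 mg weekly × 12 | 12 × 22.5 = 270 mg | all aged 13 or older, any G6PD status |
| FSAT, P. vivax, deficient | 45 mg weekly × 8 | 8 × 45 = 360 mg | G6PD deficient only |
| FSAT, P. vivax, normal | 15 mg daily × 14 | 14 × 15 = 210 mg | G6PD normal only |
| FSAT, P. falciparum | 15 mg once | 15 mg | P. falciparum cases |

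**Dose.** Weekly dose ratio: 45 / 22.5 = 2.0. Total: 360 / 270 = 1.33, so the shorter course carries a third more drug. At week 8 the totals are 360 mg and 8 × 22.5 = 180 mg. No group receives 22.5 mg weekly for 8 weeks.

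**G6PD status.** The 8-week group is entirely deficient. The MMP group has whatever mix the population has. If instead all FSAT primaquine recipients are counted, the arm pools three regimens, two of which are not weekly courses. Neither reading gives 12 versus 8 weeks.

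**How far G6PD mix alone could move a crude comparison (illustration).** These inputs are assumptions, not figures from the article: deficiency d of 5-20%, P. vivax share 30-70%, everyone aged 13 or older, hemolysis risk 10% in deficient and 0-1% in normal volunteers under any regimen. From the article: 4 FSAT clusters (8 clusters, 1:1) of 80-140, with 50% not remaining malaria free under FSAT.

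- 8-week FSAT recipients: from 4 × 80 × 0.5 × 0.3 × 0.05 = 2.4 to 4 × 140 × 0.5 × 0.7 × 0.20 = 39.2.
- MMP recipients: 4 × 80 = 320 to 4 × 140 = 560.
- Crude MMP risk, d × 0.10 + (1 − d) × risk in normals: from 0.05 × 0.10 = 0.5% to 0.20 × 0.10 + 0.80 × 0.01 = 2.8%.
- Crude risk in the 8-week FSAT group: 10%.

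Regimen has no effect in this illustration, yet the 12-week course looks several times safer.

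**Laboratory detection.** With dose 1 on day 1, the 12 MMP doses fall on days 1, 8, ..., 78. The last scheduled CBC is day 3, or day 7 after a drop above 10%.

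- MMP drug given after that: 11 × 22.5 = 247.5 of 270 mg (92%).
- FSAT 8-week drug given after that: 7 × 45 = 315 of 360 mg (88%).
- MMP doses in weeks 9-12 (days 57, 64, 71, 78): 4 × 22.5 = 90 of 270 mg (33%), with no scheduled CBC.

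For FSAT courses begun after enrollment, the early CBC rests on the wording in Clinical procedures, because Table 2 shows none in the malaria diagnosis column.

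**The case against.** The best defense is that this is a descriptive pilot safety endpoint. The objective says evaluate rather than compare, and no test, margin or duration hypothesis is given. The trial compares whole strategies, so different doses and eligibility are inherent, and the real regimens are plainly set out in Methods and Table 2. That limits the importance of the point. It does not repair the objective, which names a contrast that no analysis of these regimens can supply.

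A reader might infer that the trial will report one unstratified count per arm. The article does not say so. Strata could be set in an analysis plan that is not shown, G6PD status is measured at enrollment in those aged 13 or older, and the halting rule already counts severe hemolysis in deficient recipients. The confounding is therefore a limit on how a count by arm could be read, not a forecast of the report.

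A reader might also infer that laboratory data can say nothing about weeks 9-12. That is too strong. Clinical procedures allows testing at any time on clinical signs of hemolysis, in a sentence written for deficient volunteers, and clinical evaluations are scheduled at days 60 and 90. What is absent is a scheduled CBC, so only subclinical hemolysis is out of reach.

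Finally, the CBC rule is the same for deficient volunteers in both arms, and concentrating blood draws on those at risk is a defensible choice. If the endpoint means serious hemolysis only, the CBC point loses its force and the regimen mismatch remains.

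**Conclusion.** The point holds as a mismatch between the stated safety objective and the regimens given. Duration is confounded with a two-fold weekly dose (45 versus 22.5 mg; 360 versus 270 mg in total) and with G6PD status, so a count of events by arm cannot be read as 12 versus 8 weeks. This rests on the article's own regimens alone. The illustrative risks only show the direction and possible size of the distortion.

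The detection limit is narrower. No CBC is scheduled after about week 1, and post-dose CBCs are scheduled only for deficient volunteers, so late subclinical hemolysis would be missed while clinically apparent events could still be caught. The importance is modest: it concerns a secondary pilot endpoint and leaves the primary analysis untouched.

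**What to change.** Restate the objective with the regimens as given: 22.5 mg weekly × 12 (MMP, aged 13 or older); 45 mg weekly × 8 (FSAT, G6PD-deficient P. vivax); 15 mg daily × 14 (FSAT, G6PD-normal P. vivax); and a single 15 mg dose (FSAT, P. falciparum). Then report:

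- hemolytic events and serious adverse events by regimen and G6PD status, each with its denominator;
- hemolysis found on the scheduled early CBC, among deficient volunteers who had one, by regimen and with an exact 95% confidence interval;
- clinically detected events in all primaquine recipients, kept separate and labelled as such.

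Draw no 12- versus 8-week inference, and limit any statement about weeks 9-12 to clinically apparent events.

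This changes wording and tabulation only, with no new visit or blood draw. The price is a narrower safety statement, and some strata, above all the 8-week FSAT group, may be very small.

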### Aim and objectives

We present a pilot operational research protocol to investigate the effectiveness of monthly prophylactic drug administration compared to a focused screen-and-treat approach to inform a regional malaria elimination initiative by the Royal Cambodian Armed Forces (RCAF).*Primary objective*: to compare the effectiveness of focused screening and treatment (FSAT) following current national treatment guidelines versus monthly malaria prophylaxis (MMP) with dihydroartemisinin-piperaquine (DHA-PIP) in combination with weekly primaquine (PQ) (22.5 mg) as transmission-blocking and radical curative agent to reduce the risk of malaria infection in personnel residing in military encampments on the Thai-Cambodian border*Secondary objectives*:◦ To estimate the incremental benefit of wearing a permethrin insecticide-treated uniform (ITU) over drug therapy and existing vector control interventions compared to a sham insecticide-treated uniform (sITU) treated with water. Civilian participants will have comparable selected outer garments treated◦ To define the proportion of asymptomatic carriers of malaria in the population, including the cumulative incidence and incidence density of microscopic and submicroscopic blood-stage parasitemia and gametocytemia◦ Additional secondary objectives can be found in Table 1/Additional file 1

**Table 1 Tab1:** Outcomes

Objectives	Outcomes/endpoints
Primary	
To compare the effectiveness of focused screening and treatment (FSAT) following current national treatment guidelines versus targeted monthly malaria prophylaxis (MMP) with DHA-piperaquine in combination with low-dose weekly primaquine (PQ) (22.5 mg) for 12 weeks	Absolute risk reduction in a cluster based on those individuals’ polymerase chain reaction (PCR)-corrected absence of parasitemia at the end of 6 months in the MMP versus FSAT clusters
Secondary	
Estimate the incremental benefit of insecticide-treated uniforms (ITU) over drug therapy and existing vector control interventions compared to a sham insecticide-treated uniform (sITU)^a^	Absolute risk reduction in a cluster based on those individuals’ PCR-corrected absence of parasitemia at the end of 6 months^a^ Proportional landings of mosquitoes on treated uniform’s swatch side of cages

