### Sample size rationale

Up to 1200 persons are being enrolled and followed in this cluster-randomized study. The study compares estimates of the absolute risk reduction based on the proportion remaining malaria free at the end of 6 months. We assume that MMP administration combined with an insecticide-treated uniform (ITU) on the background of any pre-existing vector control methods that might be employed will need to reduce malaria incidence to zero by study conclusion to achieve elimination. The MMP approach will be using nearly every currently available intervention in Cambodia to eliminate malaria in this population. Current mathematical models show that multi-round mass drug administration (MDA) can reduce malaria prevalence to less than 10% if high coverage is achieved [27]. Focused screening and treatment alone (FSAT) is assumed to be 50% effective based on a recent study at the same site which found that only 50% of patients treated using an intense screening and treatment approach remained malaria free at the end of 4–6 months of follow-up [2]. The study is, therefore, powered to detect a two-fold difference in effectiveness between the two intervention groups. These are thought to be reasonable assumptions a priori for the purposes of sample size calculations though there has never been a head-to-head comparison of these strategies published in the literature. Given that this will be a stratified analysis, no assumptions regarding vector control measures are included in the calculation. Pre-existing vector control measures that the Military may employ, including ITNs, are assumed to be equally distributed among the overall study population. Permethrin-treated uniform comparisons are a secondary endpoint intended only to estimate a potential additive effect.

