### Statistical methods

The primary study endpoint will be the absolute risk reduction (ARR) with 95% confidence intervals (CIs) based on the proportion of volunteers in each arm with absence of PCR-positive parasitemia at the end of 6 months using an intention-to-treat analysis (Table 1). In addition, logistic regression modeling may be employed to provide multivariate analyses based on other possible study confounders such as age, proportion of children, proportion of pregnant women, etc. The primary study population will be intention-to-treat, defined as all volunteers (both military and civilian family members) who are enrolled at either site. The per-protocol analysis population will include all those volunteers who enrolled and completed follow-up up to 180 days. However, volunteers lost to follow-up that do not complete up to 180 days of follow-up will be excluded from the per-protocol analysis, but included in an intention-to-treat analysis.

Secondary study endpoints are pilot endpoints to include incidence rates, molecular and parasitological endpoints, safety, vector control effectiveness (e.g., permethrin-treated versus water-treated uniforms), and comparison of malaria and G6PD diagnostic modalities. The calculation of incidence rates (attack rate over total time at risk) for prophylactic and FSAT groups will be calculated adjusted and unadjusted with 95% CI. All volunteers completing at least one follow-up assessment will be included in the safety analysis. The safety analysis database will include those volunteers in the set of randomized volunteers who receive at least one dose of study drug. All parasitological data will be included in the parasitological analyses. A stratified analysis comparing the vector control arms within each group will also be compared as those remaining malaria-free at 180 days. Given the possibility of the highly variable nature of transmission at the geographical sites, existing pre-enrollment malaria surveillance data by RCAF and day 1 screening data by AFRIMS will guide if a pair-matched analysis is necessary.

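### Table 1 answers the objective on the proportion of asymptomatic carriers with incidence of parasitemia by arm, which does not estimate that proportion

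*Protocol article*

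**What the plan says.** In Table 1 (Aim and objectives), one secondary objective reads "Define the proportion of asymptomatic carriers of malaria in the study population". Its outcome cell holds one entry: "Cumulative incidence and incidence density of PCR-corrected parasitemia and submicroscopic parasitemia in each arm".

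The running text of the same section words the objective as "To define the proportion of asymptomatic carriers of malaria in the population" and continues "including the cumulative incidence and incidence density of microscopic and submicroscopic blood-stage parasitemia and gametocytemia".

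The next row of Table 1 has a different objective, "Define the epidemiology of malaria infection in volunteers developing malaria", with a very similar endpoint: "Cumulative incidence and incidence density of parasitemia".

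Statistical methods describes "incidence rates (attack rate over total time at risk) for prophylactic and FSAT groups". It names day-1 screening data only as a guide to whether a pair-matched analysis is needed.

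Under Treatment intervention and Table 2, all MMP volunteers start blood-stage drug courses on days 1, 30 and 60. In FSAT, anyone PCR-positive is treated, with or without symptoms.

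**The concern.** The objective asks for a proportion defined by two facts about a person at one time: parasites present, symptoms absent. The endpoint uses only the first fact, counts events over time, and splits the count by a treatment that acts on it.

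The Background explains why the number matters. It describes the asymptomatic group as possibly large and poorly defined, and says that large-scale implementation may be difficult or impossible in remote places if molecular testing is needed to find these people. If the Table 1 endpoint is reported as the answer, readers get two arm-specific infection rates labelled as carriage.

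The rapid-test row of Table 1 is also affected. Its outcome is the share of asymptomatic carriers each test would have missed, so it needs the same group to be defined.

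**Working it through.** The document attaches no sample size, precision target or expected prevalence to this objective, so there is no figure to reproduce. The check sets the objective and endpoint side by side.

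**1. Symptoms.** Let I be the cumulative incidence of PCR-positive parasitemia and s the share of those infections that are symptomatic. Volunteers with an asymptomatic infection make up I × (1 − s). The endpoint reports I whatever s is. The document gives no s. For assumed values of 10%, 50% and 90%, the asymptomatic part is 0.90 × I, 0.50 × I and 0.10 × I, and the reported figure is the same each time. The submicroscopic component helps only in part: it omits smear-positive volunteers who feel well and can include smear-negative volunteers who are ill. Treatment intervention itself treats PCR-only detection and freedom from symptoms as two separate conditions in the MMP arm.

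**2. Type of quantity.** A carrier proportion is (symptom-free PCR-positives at a time) / (people tested at that time). Incidence density is (events) / (time at risk). Cumulative incidence is (people with an event during a period) / (people followed). The text does not say how day-1 positives enter the last two.
- If they are not counted, carriers present at enrolment are absent from the measure.
- If they are counted, cumulative incidence mixes carriage at enrolment with infections acquired over six months.

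Neither reading gives the proportion carrying parasites.

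**3. By arm, under treatment.** MMP volunteers receive drug from day 1 regardless of test result. FSAT volunteers are treated once PCR detects infection. Follow-up in both arms is therefore modified by the assigned strategy. The Limitations section states the hypothesis that MMP lowers risk further than FSAT; if so, the two arm values will differ, and neither, nor their average, describes the untreated population.

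**4. Other places that might supply the proportion.**
- The continuation in the running text adds incidence measures to the objective. It gives no symptom rule, time point or denominator.
- Statistical methods says that all parasitological data enter the parasitological analyses. That concerns which data are used, not what is estimated.
- The abstract says monthly screening compares tests for detecting asymptomatic infection. That is a diagnostic purpose.
- The rapid-test row takes carriers as its denominator. It does not give carriers as a share of the population.

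**5. Can the right quantity be obtained?** Yes. Table 2 marks medical history, physical examination, rapid test, smear and PCR at enrolment. Clinical procedures gives every volunteer an enrolment history and examination, and gives children aged 12 and under rapid test, smear and PCR. Two details need fixing in words. Table 2 marks the brief clinical evaluation and vital signs only from day 30, so day-1 symptom status must come from the enrolment history and examination. Table 2 also marks treatment on day 1, so the sample must be specified as pre-dose.

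**The case against.** The strongest reply is that the running text names the proportion as the objective and lists incidence as part of it, so incidence need not replace the proportion. The trial also has to identify symptom-free positives for its rapid-test comparison, and a condensed article may leave the carrier definition to the full protocol or the analysis plan. This is fair as to detail. It does not remove the mismatch, because Table 1 states an endpoint, it is the only one in that row, and it is a different quantity from the objective.

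Three stronger readings are tempting and are not supported.

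- A reader might infer that day-1 carriers are excluded. The terms incidence and time at risk suggest it, but no sentence says so, and the statement that all parasitological data are used points the other way.
- A reader might take the planning values in Sample size rationale to predict about 50% in FSAT against 0% in MMP. The MMP assumption is that the strategy "will need to reduce malaria incidence to zero by study conclusion to achieve elimination", an end state and not zero cumulative incidence over six months. The FSAT 50% comes from treated patients in an earlier study and is used to power the primary endpoint.
- A reader might conclude that the endpoint mainly reflects drug strategy. Both strategies alter it, but the document does not allow that share to be quantified.

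It is also fair that reporting by arm is natural in a two-arm trial and that the epidemiology row is not identical: it concerns volunteers who develop malaria and does not list submicroscopic parasitemia separately. The overlap between the rows is a secondary observation.

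**Conclusion.** The point holds as a mismatch between a stated objective and its stated endpoint. It rests on the wording of Table 1 and on the treatment rules in both arms, not on any assumed rate. Its numerical size is unknown: the symptomatic shares used above are assumptions that show only that the endpoint does not respond to symptom status. The treatment of day-1 positives is an open question, and the conclusion stands on either answer.

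The weight is modest. The endpoint is secondary and descriptive, the article calls its secondary endpoints pilot endpoints, and no power calculation or decision rule depends on this row. The primary comparison is untouched.

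**What to change.** In Table 1, replace the endpoint for this objective with the following: the prevalence on day 1, before the first study dose, of PCR-positive parasitemia (any, and smear-negative) in volunteers without fever or malaria symptoms. The denominator is all enrolled volunteers with a day-1 PCR, both arms combined, with a confidence interval that allows for the eight clusters. Name the enrolment history and examination as the source of symptom status.

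Report symptom-free PCR-positive prevalence by arm at each monthly visit as a separate description. Keep cumulative incidence and incidence density under the epidemiology objective, and state there how day-1 positives are handled. Use the same carrier definition for the rapid-test row.

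The cost is a change of wording and one extra table. No added sample, visit or volunteer is needed.
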